## Abstract

**Background:**

Functional constipation (FC) is a common functional gastrointestinal disorders (FGIDs) which has a major impact on the quality of life. Acupuncture is widely used as an alternative and complementary medicine (CAM) for FC, but the available evidence of its effectiveness is scarce. Therefore, we will perform a randomized controlled trial to determine whether acupuncture improves symptom and quality of life in FC patients more effectively than sham acupuncture or gastrointestinal prokinetic agent. This article will report the protocol of the trial.

**Methods:**

The current trial is a multicenter, randomized, three-arm controlled study undergoing in China. About 243 people who aged from 18 to 65 years with FC will be recruited in this study. These participants will be randomly allocated into three treatment groups, including electro-acupuncture (EA), Mosapride (M) and Mosapride & Sham Electro-acupuncture (MS) groups in a 1:1:1 ratio. Both the EA and sham EA receives 16 sessions of needling at Quchi (LI11) and Shangjuxu (ST37) during 4 weeks of treatment, and a follow-up period of 4 weeks. These groups will be compared on the primary outcomes of the number of times of defecation at baseline and 2, 4, 8 weeks after randomization. The secondary outcome measures include: stool consistency, intensity of defecating difficulty, MOS item Short Form health survey (SF-36), Self-Rating Anxiety Scale (SAS), Self-rating Depression Scale (SDS), and the validated Patient Assessment of Constipation Quality of Life (PAC-QOL). These outcomes are measured at baseline and 2, 4 weeks after randomization, but SF-36 is measured at baseline and 4 weeks after randomization.

**Discussion:**

This study will supply significant evidence for using acupuncture to treat FC, and will help us to observe whether it is a therapeutic effect rather than a placebo effect.

## Background

Functional constipation (FC) is a common functional gastrointestinal disorders (FGIDs), defined as infrequent bowel movements, hard or lumpy stools, straining during defecation that does not meet the IBS criteria
[1]. According to the survey, about 12%-19% population in the US and 14% in Asia suffer from the symptoms of functional constipation
[2–4]. As a major public health issue, functional constipation negatively affects health-related quality of life and is associated with substantial costs.

Usual care involves lifestyle modification such as dietary changes and aerobic activities are recommended to help in relieving symptoms but some studies have suggested that the effect is not obviously
[5, 6]. In recent years, conventional treatments include gastrointestinal prokinetic agent, enemas, osmotic and stimulant laxatives has displayed a positive effect in functional constipation therapy. However, the efficacy is limited and unwanted side effects are induced with a long therapeutic course
[7].

More and more people have focused on alternative and complementary medicine (CAM) to look for a safe and effective therapy for functional constipation in Western countries
[8]. Acupuncture as one of the most frequently applied methods in Traditional Chinese Medicine (TCM), which has a history of more than 3000 years in treating functional constipation, has gained increased popularity. Previous studies have shown that acupuncture may be effective in the treatment of functional constipation but have not provided conclusive evidence of its efficacy. An appropriate trial protocol is needed to investigate the effectiveness of acupuncture for functional constipation. Thus we designed a multicenter randomized controlled trial to observe and testify the clinical effects of acupuncture for FC. Meanwhile, we aim to address whether acupuncture treatment is the better therapy compared with medication treatment.

## Methods and Design

### Design

This is a multicenter randomized controlled, three-arm trial enrolling both men and women with functional constipation in China. This study will be conducted at Tongji Hospital affiliated to Tongji Medical College, Huazhong University of Science and Technology; Hubei Provincial Hospital of TCM; Hospital of Huazhong University of Science and Technology. Tongji Hospital is the central structure of the study. The participants will be allocated through complete randomization in a 1:1:1 ratio. The randomization sequence will be generated using R2.0 software. A designated researcher will prepare the assignments in opaque envelopes in sequence. The acupuncturists will only know of the group assignment prior to the treatment.

This trial is financed by the National Basic Research Program (No. 2011CB505203). The research protocol has been approved by the Clinical Trial Ethics Committee of Tongji Medical College, Huazhong University of Science and Technology (approval no. FWA00007304) and registered on the ClinicalTrials.gov protocol registration system (
http://clinicaltrials.gov/ct2/show/NCT01781897, ClinicalTrials.gov ID: NCT01781897).The duration of this study is 9 weeks for each patient: a screening period of 1 week, a treatment period of 4 weeks, and a follow-up period of 4 weeks. Constipation diaries are required to record at least 1 week before randomization as baseline data and this course will be continue to 8 weeks if they are eligible for this trial. All outcomes are assessed at baseline and 2, 4, and 8 weeks after randomization according to the diaries. A total of 16 sessions of acupuncture treatment will performed over a period of 4 weeks and each session will last 30 min after randomization. Five times a week in the first 2 weeks and three times a week in the last 2 weeks (Figure 
1).

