### Sample size calculation

Sample size was determined based on a study
[15] where the average defecation rate of patients with functional constipation was 2.6 times per week with a standard deviation of 2.2 after drug treatment, and a 1.4-fold difference in the clinical effects between the drug and the placebo is considered to be of clinical relevance. In this study, we anticipated that an improvement of the mean defecating frequency is 4.0 after acupuncture treatment, with a standard deviation of 3. To detect this difference, we need a sample size of 71 in each group (α = 0.05, β = 0.10)
[16]. To allow 15% for loss to follow up, our proposed trial requires 243 patients (81 for each group).

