### Statistical analysis

Statistical analysis of all data will be done by the Department of Epidemiology and Biostatistics, School of Public Health, Tongji Medical College, Huazhong University of Science and Technology, which is blinded to this trial. SPSS 17.0 software packages will be used to analyze the data. All data are provided as mean ± standard deviation (SD) in continuous data and as frequency/percentage in categorical data. All of the analyses will be based on both an intention-to-treat analysis (ITT) and a treated-per-protocol analysis (TPP). The intention-to-treat (ITT) population was defined as the patients who are randomized and received at least one treatment session. The missing data will be dealt with the last observation value carried forward (LOCF) method. The per-protocol (PP) population was defined as the patients who have no major protocol violations in the ITT set. Both results of analysis will be compared to check whether the results are consistent.

Comparisons among baseline characteristics in different groups will be analyzed at first by analysis of variance, Chi-square test, and others. Then analysis will be applied to compare the effects of intervention between groups. Chi-square test will be used for comparison of categorical variables and analysis of variance of repeated measures will be performed for continuous parameters between the groups. The level of significance was set a P value less than 0.05.

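### Complete randomisation over three hospitals, with no stratum, block or hospital term named, does not guarantee 81 per group or balance within hospitals; the cost is small and the remedy cheap

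*Protocol article*

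**What the plan says.** All references are to the protocol article.

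- **Design:** "This is a multicenter randomized controlled, three-arm trial enrolling both men and women with functional constipation in China". Three hospitals are named, with no recruitment target for any of them.
- **Design, allocation:** "The participants will be allocated through complete randomization in a 1:1:1 ratio". The list is produced in R, and on concealment the section says: "A designated researcher will prepare the assignments in opaque envelopes in sequence". No block size or stratification factor is given, and the text does not say whether there is one list or one per hospital.
- **Sample size calculation:** 71 evaluable patients per group, raised for 15% loss to 243 in total, "81 for each group".
- **Statistical analysis:** "analysis of variance of repeated measures will be performed for continuous parameters between the groups". Hospital is not mentioned as a factor, but neither is it said to be left out.

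**The concern.** Complete randomisation ordinarily means that each patient is assigned independently with probability one third. Arm sizes are then random, both overall and within each hospital, while the sample size is planned as three equal groups.

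Hospital could plausibly matter here. The sites are of different kinds, and the Recruitment procedures section draws patients from clinics, community hospitals, a newspaper and a website. The needling is manual, with current adjusted to patient comfort. If outcomes differ by hospital and the arms have different hospital mixes, an analysis without hospital carries that variation in its error. A reader of the results may also ask how much of an observed difference reflects site.

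**Working it through.** **1. The plan's own figures.** Inputs from the Sample size calculation section: means 4.0 and 2.6 (difference 1.4), SDs 3 and 2.2, α = 0.05, power 90%.

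- With the average SD of 2.6 and a two-sided test, n = 2 × 2.6² × (1.960 + 1.282)² / 1.4² = 72.5, so 73 per group, close to the stated 71.
- 71 × 1.15 = 81.65, which truncates to the stated 81. (Dividing, 71 / 0.85, gives 84; that is a separate matter.)

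**2. Overall arm sizes under literal complete randomisation.** Sizes are multinomial (243; 1/3, 1/3, 1/3).

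- SD of one arm = √(243 × 1/3 × 2/3) = 7.3; 95% range about 67 to 96.
- P(exactly 81/81/81) = 243! / (81!)³ / 3²⁴³ = 0.34%.
- Median gap between largest and smallest arm: 14 (400,000 simulated allocations).
- P(at least one of three arms below 71) = 22%. For any one named arm it is 7.5%.

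**3. What this costs in power.** Power = Φ(1.4 / √(2.2²/n₁ + 3²/n₂) − 1.960), with n₁ and n₂ reduced by 15%.

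- Fixed at 81: n = 81 × 0.85 = 68.85, SE = √(13.84 / 68.85) = 0.448, 1.4 / 0.448 = 3.12, power 87.75%.
- Averaged over complete randomisation: about 87.5% (95% range 83.8% to 90.4%).
- Mean loss: about 0.3 points.

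**4. Balance within a hospital.** Hospital sizes are not in the document, so these are assumed. The shuffled list is the other possible reading: one list with exactly 81 slots per arm, giving hypergeometric counts within a hospital.

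| Patients in hospital (assumed) | Largest ≥ 1.5 × smallest, unrestricted | Same, shuffled list | Largest ≥ 2 × smallest, unrestricted |
|---|---|---|---|
| 20 | 78.5% | 77% | 48% |
| 40 | 57% | 51% | 22% |
| 81 | 31% | 18% | 4% |
| 120 | 18% | 4% | 1% |

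The shuffled list fixes the totals at full recruitment but not the split within hospitals, although the problem shrinks quickly in a large hospital.

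**5. What this could do to one realised estimate.** For assumed hospital splits from 81/81/81 to 183/40/20, one hospital's share of patients differs between two arms by more than 10 percentage points in 14% to 20% of unrestricted allocations. If that hospital's mean differed from the rest by 1 defecation per week (assumed), a 10-point gap would move the unadjusted difference by 0.10 × 1 = 0.10. At 0.5 or 2 per week it would be 0.05 or 0.20. These compare with a planned difference of 1.4 and an SE of 0.448.

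**The case against.** Four points can fairly be made against this.

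- **The totals.** 81 is a planning target, and the Abstract speaks of about 243 people. A pre-generated sequence in a 1:1:1 ratio also fits a shuffled list with 81 slots per arm. A reader might infer that the plan cannot deliver 81 per group. The text does not support that: under one reading 81 is the expected size, under the other it is exact at full recruitment. This stands.
- **The analysis.** A reader might infer that hospital is excluded from the model. The article only fails to name it, and a condensed article commonly leaves covariates to a fuller document. This stands, so the analysis half is a request to fix and state the factor, not a finding of omission.
- **Bias and mechanism.** A reader might infer that chance imbalance by hospital biases the treatment effect, or that needling skill is known to differ by site. Neither follows. Randomisation keeps the comparison unbiased, and chance imbalance is part of its sampling error. The article gives no between-hospital variance, and its Quality control section requires training, a qualifying test and monthly inspection. This stands too.
- **Predictability.** Acupuncturists know past assignments, so the least predictable scheme is a defensible choice. This is a real trade-off, but random, undisclosed block sizes limit it, and it does not touch the hospital factor in the model.

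What remains is that, with no stratum named, neither reading of the allocation wording secures balance within hospitals, and adjustment would cost almost nothing.

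**Conclusion.** The point holds in a narrow form and is minor. As stated, the allocation does not guarantee 81 per group if read literally, and does not secure balance within hospitals under either reading. The overall consequence is slight, about 0.3 points of mean power. The within-hospital imbalance depends on assumed hospital sizes and matters mainly for small sites. It costs precision and credibility only to the extent that outcomes differ by hospital, which the document does not quantify. The conclusion assumes that no hospital-specific list exists. If there is one list per hospital with equal slots per arm, allocation is already stratified and the article need only say so.

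**What to change.** 1. **Model.** Include hospital as a fixed factor (main effect) in the primary repeated-measures analysis, and fix this before unblinding. It uses two degrees of freedom, needs no new data, and also adjusts for imbalance among patients already randomised.
2. **Allocation of patients still to be recruited.** The Trial status section says recruitment was under way. Use permuted blocks of random, undisclosed size (multiples of three), stratified by hospital, with the list held away from the acupuncturists. This holds arms near-equal within each hospital, apart from an incomplete last block. It costs a new list and slightly more predictable allocation, because acupuncturists know past assignments. Patients already randomised keep their assignment.
3. **Wording.** State whether the existing sequence is unrestricted or a shuffled list with fixed totals, and whether there is one list or one per hospital. If recruitment has closed, steps 1 and 3 are what remains.

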**Figure 1 Fig1:**
[figure not shown]
**Trial flow chart.**

## Patients

### Study population

Our study will include patients with chronic functional constipation. To ensure the precision of results of this trial, patients who meet the following eligible criteria will be included in this study.

### Inclusion criteria

Men and women between 18 and 65 years old who met the Rome III Criteria for functional constipation (FC), including two or more of the following symptoms for at least 12 weeks during the 6 months before enrolling the study: (1) straining during at least 25% of defecations; (2) lumpy or hard stools during at least 25% of defecations; (3) sensation of incomplete evacuation during at least 25% of defecations. (4) Sensation of anorectal obstruction or blockage for at least 25% of defecation; (5) Manual maneuvers to facilitate at least 25% of defecation (e.g. support of fingers or pelvic floor); (6) fewer than three spontaneous bowel movements (SBMs) per week. And (1) loose stools are rarely present without the use of laxatives, (2) insufficient criteria for irritable bowel syndrome are necessary. Meanwhile we must confirm all the participants did not use any gastrointestinal drugs at least 1 week before randomization and never joined any other trial in progress. They signed a written consent form and volunteered to finish the whole study.

### Exclusion criteria

Patients with any of the following conditions will be excluded: constipation caused by other endocrine, metabolic, nervous or postoperative diseases or drugs; irritable bowel syndrome (IBS) and inflammatory bowel disease or other structural bowel diseases; psychiatric diseases and cognitive dysfunction or aphasia; tumours and bleeding disorders; serious illnesses of the heart, liver, or kidney, or other severe diseases; pregnant or breastfeeding women; other disorders that may interfere with completion of the study.

### Recruitment procedures

Participants will be recruited in outpatient clinics of hospitals or community hospitals. Participants will also be recruited through local newspaper and the hospital website (
http://www.tjh.com.cn/). Doctors from gastrointestinal surgery and gastroenterology department of the local hospitals would be invited to screen participants.

## Interventions

### Electro-acupuncture (EA) group

The acupuncture treatment bases on traditional Chinese medicine theory and should be operated by licensed acupuncturists. The acupoints are Quchi (LI11) and Shangjuxu(ST37), which are He-Sea and Lower He-Sea acupoints of Large Intestine meridians. Both points were considered as the positive points to treat internal organ’s disease in traditional Chinese medicine (TCM) and were very commonly used in FC patients. Sterile, disposable acupuncture (0.25 mm in diameter and 40 mm in length) are used in this trial, which are purchased from DongBang AcuPrime. Ltd. Co (Marsh Barton, Exeter, UK). In this group, the fixed points will be inserted bilaterally and vertically by filiform needles after sterilizing. A dull needling sensation (which called *de qi* include sour, numb, heavy and aching) will be obtained through lifting, thrusting, twirling and rotating the needles. And then, an electro-acupuncture instrument (HANS-200E, Nanjing Jisheng, made in Jiangsu, China) will connect with each acupuncture needle. The stimulation frequency set 2/50Hz and electric current varies from 0.1 mA to 1.0 mA until the patients feel comfortable. Each session will last for 30 minutes per day. A total of 16 sessions of acupuncture treatment will perform over a period of 4 weeks. Five times a week in the first 2 weeks and three times a week in the last 2 weeks.

### Mosapride (M) group

Participants assigned to this group will receive 5 mg Mosapride Citrate tablet (Dainippon Sumitomo pharmaceutical Co.Ltd, Japan) three times a day for 4 weeks continuously, in the form of an oral capsule administered at least 30 minutes before eating.

### Mosapride & Sham Electro-acupuncture (MS) group

The participants appointed to mosapride & sham acupuncture group will be treated with sham acupuncture while orally given Mosapride Citrate tablets (Dainippon Sumitomo pharmaceutical Co.Ltd, Japan). The dose of mosapride is 5 mg three times a day for 4 weeks continuously as the same as mosapride (M) group. In the sham acupuncture intervention, Park sham devices (PSD)
[9] are used, which are purchased from DongBang AcuPrime. Ltd. Co (Marsh Barton, Exeter, UK). It is a non-penetrating needle device with a blunt and retractable needle, a guide tube and a self adhesive pad. The fixed points are bilateral Quchi (LI11) and Shangjuxu (ST37), which are also the same as the treatment group. A precut guide tube which is fixed by a self adhesive pad was slightly depressed down onto the selected point. And then, the blunt sham needle is carefully placed into the guide tube. When pressed, it telescopes into the handle and induces a pricking sensation rather than penetrates the skin. During this process, no twirling lifting and thrusting manipulation is conducted. The sham electro-acupuncture instrument is applied to the needles but the metal inside the wire has been cut off. We set a stimulation frequency of 2/50 Hz and electric current of 0.3 mA but actually, there is no current output and the participants will never know.

### Outcome measures

The primary outcomes of the study is the times of defecation per week at baseline and at the 2nd, 4th and 8th week after randomization. Secondary efficacy end points include: 1) stool consistency
[10]; 2) intensity of defecating difficulty; 3) MOS item Short Form health survey (SF-36)
[11]; 4) Self-Rating Anxiety Scale (SAS)
[12]; 5) Self-rating Depression Scale (SDS)
[13]; 6) the validated Patient Assessment of Constipation Quality of Life (PAC-QOL)
[14] (Table 
1).

**Table 1 Tab1:** **Trial processes chart**

Week	-1	0	2	4	8
	Baseline	Treatment			Follow-up
**Patients**					
Medical history	√				
Physical examination	√	√	√	√	
Laboratory examination	√			√	
Informed consent		√			
Randomization		√			
Expectation of acupuncture		√			
**Intervention**					
Electro-acupuncture (EA) group	16 sessions of electro-acupuncture				
Mosapride (M) group	5 mg mosapride citrate tablet, three times a day				
Mosapride & Sham	16 sessions of sham electro-acupuncture and 5 mg mosapride citrate tablet, three times a day				
Electro-acupuncture (MS) group					
**Outcomes**					
Number of defecating events per week		√	√	√	√
Shape and properties of stool		√	√	√	√
Intensity of defecating difficulty		√	√	√	√
SF-36		√		√	
SAS		√	√	√	
SDS		√	√	√	
PAC-QOL		√	√	√	√
**Trial evaluation**					
Safety of electro-acupuncture		√	√	√	
Adverse event		√	√	√	
Reasons of drop-outs or withdrawals				√	
Patient’s compliance				√	

SF-36, MOS item Short Form health survey; SAS, Self-Rating Anxiety Scale; SDS, Self-rating Depression Scale; PAC-QOL, patient assessment of constipation quality of life questionnaire.

The first three outcomes will be measured at the other time points (baseline and 2, 4, 8 weeks after randomization) according to the daily records written by participants. Stool consistency was assessed by the Bristol Stool Form Scale (BSFS)
[10]. Intensity of defecating difficulty was assessed by a 4-point scale with the following responses: 0 indicates not at all, 1 a little bit, 2 a moderate amount, 3 a great deal and an extreme amount. PAC-QOL include 28 items related to the effects of constipation on daily lives. These outcomes will be measured at baseline and 2, 4, 8 weeks after randomization which provided by participants. Patients are asked to complete the SAS and SDS questionnaire at baseline and 2 and 4 weeks after randomization. SF-36 questionnaire is completed before randomization and 4 weeks after randomization.

Before randomization all patients will receive routine tests of urine, stool, blood biochemical (ALT, AST, BUN, and Scr), electrocardiogram (ECG), and colonoscopy to exclude these patients who have other severe diseases. Urine HCG or blood β-HCG will also be tested to exclude possible pregnant women. These routine tests should also be done after accomplishment of intervention to help us assess the adverse events.

Adverse events including bleeding, hematoma, fainting, serious pain, and local infection should be recorded and resolved immediately during all duration of this study. Serious adverse events will be documented and immediately reported to the principal investigator.

